#### DMC oversight

The independent Data Monitoring Committee (DMC) conducts a scheduled safety review 1 week after completion of treatment in the third participant of each cohort. This timing is considered adequate for capturing clinically relevant early grade ≥3 drug‑related adverse events as sulfasalazine is administered for only three days, has a plasma half‑life of approximately 12.7 h, and is known to cause early rather than delayed toxicity. However, any grade ≥3 adverse events occurring after the initial review within the DLT window will trigger an additional DMC assessment during which enrollment will be paused. Such events may result in cohort expansion or dose de‑escalation as appropriate.

In accordance with standard practice in phase I trials combining systemic agents with radiotherapy, late toxicities will not contribute to dose‑escalation decisions because they occur too long after investigational drug exposure to inform MTD determination. Nevertheless, clinically meaningful late radiation‑induced adverse effects, including those potentially modified by radiosensitization and typically emerging months to years after treatment, will be documented and monitored throughout longitudinal follow‑up

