### Study design

This is a phase I, single‑center dose‑escalation trial using a classic 3 + 3 design [17] to evaluate escalating doses of oral sulfasalazine administered for three days prior to GKRS with an anticipated recruitment period of 24 months. The dose will be escalated or de-escalated with diminishing fractions of the preceding dose (modified Fibonacci sequence), depending on the occurrence of adverse events grade ≥ 3.

Cohorts of three patients receive escalating once‑daily sulfasalazine doses (1.5, 3, 4.5, 6 g) for three days, with GKRS on Day 3. Escalation proceeds if no ≥ grade 3 toxicity occurs; a single ≥ grade 3 event expands the cohort to six; ≥2 events at a dose level in 3–6 participants define that dose as exceeding the maximum tolerated dose (MTD), with the preceding dose as the recommended phase 2 dose.

Each participant undergoes a three‑day treatment phase followed by clinical and radiological follow‑up for up to one year. This design allows systematic dose escalation while ensuring patient safety and assessment of early efficacy signals.

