### Intervention

Participants are admitted to the hospital for five days, from Monday to Friday. Screening procedures and baseline assessments are conducted on the day of admission (Day 0). The intervention takes place over the subsequent three days (Day 1–3), and participants are discharged on Day 4 following an end‑of‑treatment safety evaluation.

During the intervention period, participants receive oral sulfasalazine in the form of enteric‑coated 500 mg tablets administered once daily for three consecutive days. Dose escalation follows a traditional 3 + 3 design, in which cohorts of three to six participants receive one of four predefined dose levels: 1.5 *g*, 3 *g*, 4.5 *g*, or 6 *g* once daily. All doses are administered under the supervision of a study nurse, who monitors intake and assesses acute tolerability.

On the third intervention day, approximately 6 hours after participants receive their third and final sulfasalazine dose, they undergo stereotactic gamma knife radiosurgery. GKRS is delivered with a standard prescription dose of 12 Gy to the contrast‑enhancing tumor volume.

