To ensure adequate safety maturation, a minimum of 1 week must elapse after the completion of treatment on Day 3 in the preceding participant before the next participant is enrolled. Missed doses, dose reductions and early discontinuation will not remove a participant from DLT evaluability. Hospitalization does not remove a participant from DLT evaluability unless it is due to a pre‑planned elective procedure or expected disease progression rather than an adverse event related to sulfasalazine or GKRS. Serious adverse events (SAEs) will be reported according to regulatory timelines. Late radiation‑related toxicity will be monitored at 3, 6, 9 and 12 months post-GKRS, but will not influence dose‑escalation decisions.

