#### Response assessment

Tumor response versus treatment‑related change is assessed on longitudinal MRI per RANO 2.0[31], which requires a confirmation step to reduce misclassification of early post‑treatment effects. New or increasing enhancement on follow‑up is therefore classified as preliminary progression until a confirmatory MRI at 6–8 weeks determines confirmed PD or confirmed pseudoprogression, with the final status backdated to the preliminary timepoint. If MRI follow‑up remains inconclusive, amino‑acid PET may be used.

Pseudoprogression is defined as an early, transient treatment‑related imaging change that typically occurs within 12 weeks after radiation and stabilizes or improves without a change in therapy.

Radionecrosis is defined as a late, progressive radiation‑induced tissue injury occurring months to years after radiotherapy. Histopathology is the reference standard when resection is performed but is not required for diagnosis. All MRI timepoints are read centrally by an experienced academic neuroradiologist, independent of the treating team and blinded to the sulfasalazine dose level, ensuring consistent, unbiased interpretation across participants.

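### Late toxicity is barred from escalation decisions, so 4.5 g and 6 g can open without DMC review of late grade ≥3 events already recorded

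*Protocol article*

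**What the plan says.** Two sections of the article give the same rule. Under Primary outcome: "Late radiation‑related toxicity will be monitored at 3, 6, 9 and 12 months post-GKRS, but will not influence dose‑escalation decisions". Under DMC oversight, with a reason: "late toxicities will not contribute to dose‑escalation decisions because they occur too long after investigational drug exposure to inform MTD determination".

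The DMC has two defined review points:

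- A scheduled review, one week after the third participant of a cohort completes treatment. Its timing is justified by the 12.7 h half-life and by early drug toxicity.
- An event-driven review with a pause in enrolment: "any grade ≥3 adverse events occurring after the initial review within the DLT window will trigger an additional DMC assessment". The window closes 30 days after Day 3 (Primary outcome).

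Late effects, "including those potentially modified by radiosensitization and typically emerging months to years after treatment", are to be recorded and followed, with no DMC step attached. Response assessment adds: "Radionecrosis is defined as a late, progressive radiation‑induced tissue injury occurring months to years after radiotherapy". The Limitations section accepts that radiation side effects mostly appear after 30 days.

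**The concern.** The stated reason (short half-life, long delay after drug exposure) fits direct drug toxicity. It does not fit the harm this combination could plausibly add. Sulfasalazine is given to strengthen the radiation effect on Day 3, and excess injury to previously irradiated brain would show months later. On the article's own definition, radionecrosis falls outside the DLT window.

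This leaves an asymmetry. Two related grade ≥3 events among 3 to 6 participants inside the window mark a dose as too high (Study design). The same two events after the window are stated to have no bearing on opening the next dose. Followed as written, new participants could receive 4.5 g or 6 g when serious late injury is already on file at 1.5 g or 3 g. The DMC need not have seen it, and the plan does not let escalation respond to it.

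The exclusion of late events from the DLT and MTD definitions is not in dispute.

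**Working it through.** **Inputs.** Four dose levels in cohorts of 3 to 6 (Intervention); 12–24 participants (Sample size); "an anticipated recruitment period of 24 months" (Study design); at least one week between Day 3 of one participant and enrolment of the next (Primary outcome); "Participants are admitted to the hospital for five days, from Monday to Friday" (Intervention). Justification for prescription dose cites a 77-patient series (median 12 Gy, range 8–20) with median PFS 6 months, median OS 12 months and no radionecrosis.

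**1. The plan's own figure.** 4 × 3 = 12 and 4 × 6 = 24, so the enrolment range reproduces.

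**2. Follow-up on hand when each level opens.** Assume even accrual with no gaps between levels. Spacing is 24/12 = 2 months (3 per level) or 24/24 = 1 month (6 per level). Either way, levels 2, 3 and 4 open at months 6, 12 and 18. Time since entry is then 2, 4, 6, … or 1, 2, 3, … months. Because GKRS falls on Day 3, a participant at exactly 3 or 6 months from entry is not counted.

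**3. Attrition.** Scheduled clinical and MRI follow-up can end at progression (Secondary outcomes), so counts are scaled by S(t) = 0.5^(t/median), an exponential assumption. With PFS median 6, S(3) = 0.707 and S(6) = 0.500. If late toxicity is instead followed in all survivors, OS median 12 gives S(3) = 0.841 and S(6) = 0.707.

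| Level opening | Past 3 mo | Past 6 mo | Reach 3 / 6 mo progression-free | Reach 3 / 6 mo alive |
|---|---|---|---|---|
| 3 g (month 6) | 2 of 3 or 3 of 6 | 0 | 1.4–2.1 / 0 | 1.7–2.5 / 0 |
| 4.5 g (month 12) | 5 of 6 or 9 of 12 | 3 or 6 | 3.5–6.4 / 1.5–3.0 | 4.2–7.6 / 2.1–4.2 |
| 6 g (month 18) | 8 of 9 or 15 of 18 | 6 or 12 | 5.7–10.6 / 3.0–6.0 | 6.7–12.6 / 4.2–8.5 |

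Columns 2 and 3 are maxima before attrition. When 6 g opens, the 3 g participants are at 12, 10, 8 months (12 participants) or 12, 11, 10, 9, 8, 7 months (24 participants), if alive.

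**4. Fastest accrual.** Monday admission puts Day 3 on Thursday. Seven more days lead to the following Thursday, and the next Monday is day 14. At 14-day spacing, unadjusted counts more than 91 days past GKRS are 0, 0, 3 (3 per level) or 0, 6, 12 (6 per level) when levels 2, 3 and 4 open. Counts more than 183 days past are 0, 0, 0 or 0, 0, 5.

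**5. How surprising late events would be.** For 0 of 77, the one-sided 95% upper bound is 1 − 0.05^(1/77) = 0.0382. Binomial probabilities at that rate:

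| n | P(≥1) | P(≥2) |
|---|---|---|
| 3 | 11% | 0.4% |
| 6 | 21% | 2.0% |
| 11 | 35% | 6.4% |
| 15 | 44% | 11% |

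The row n = 11 rounds the 10.6 above, and n = 15 is the unadjusted maximum; both pool dose levels.

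**6. If the true late rate were higher.** The article gives no late grade ≥3 rate for the combination, so these rates are assumed. With full follow-up and no deaths, the chance of at least two events among 6 participants is 3% at a 5% rate, 11% at 10%, 35% at 20% and 77% at 40%. Among 9 it is 7%, 23%, 56% and 93%.

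**The case against.** The strongest reply has four parts.

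- **It is declared.** The article states the rule, gives a reason, calls it standard practice and lists late effects as a limitation partly offset by surveillance. This justifies leaving late events out of the MTD. It does not explain why recorded late events should have no influence on exposing new participants to a higher dose.
- **Nothing forbids the DMC from seeing late data.** It has a general safety remit (Data management and analysis), and the contents of its reports usually sit in a charter. That stands: review is not required, rather than prohibited. But two explicit sentences deny late toxicity any role in escalation, and a general remit does not override them.
- **Other routes exist.** Necrosis needing surgery would ordinarily be reported as an SAE, and expected GKRS effects become SUSARs if more severe or more frequent than anticipated (Primary outcome). A cluster might well be noticed. However, SAE reports concern single events, judging frequency needs a cumulative view by dose, and neither route is tied to opening a level.
- **The evidence would be thin.** There is no control arm, salvage treatment confounds, and new enhancement needs a confirmatory MRI at 6–8 weeks. The 3.8% bound comes from a rough reference for radionecrosis only, not edema. Applying all of it to participants just past 3 months overstates the chance of events at that reference rate. The n = 11 and n = 15 figures pool doses, whereas the in-window rule works per level. All of this stands, and it argues for DMC judgement rather than an automatic rule.

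**Conclusion.** The concern holds and should be corrected. The rule is stated outright, and it excludes from escalation the class of harm that a radiosensitizer could plausibly add. On the planned calendar the delay argument fails for the upper levels: about 3.5–7.6 earlier participants are expected to have reached 3 months when 4.5 g opens and 5.7–12.6 when 6 g opens, across both attrition assumptions. Before 3 g, or under fast accrual, little late information exists and the gain is small. One late event would be weak evidence; two or more would be unexpected against the rough reference (2.0% for n = 6, 6.4% for n = 11).

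The counts rest on even accrual without gaps and on exponential PFS and OS at the cited medians. Confidence is moderate, because the full protocol and any DMC charter are not shown.

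**What to change.** Under Primary outcome, replace the clause denying late toxicity any influence on escalation with: *will not count as DLTs or define the MTD, but will be reviewed by the DMC before each new dose level opens*. Align the matching sentence under DMC oversight.

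At each cohort review, give the DMC one cumulative table by dose level. It should show post-window grade ≥3 events at least possibly related to sulfasalazine or GKRS, including symptomatic edema and radionecrosis needing surgery, with the numbers followed to 3, 6, 9 and 12 months. Leave the DMC free to hold escalation, with no automatic pause for a single late event.

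The DLT window, MTD rule and sample size stay as they are. The late visits, MRIs and central reads are already planned, as is a summary of grade ≥3 events by cohort, so no extra patients or procedures are needed. The cost is slightly more DMC reporting and an occasional delay if escalation is held on sparse data, for example while a confirmatory MRI is awaited.

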#### Secondary outcomes

Secondary outcome assessments will include clinical (KPS/FACT-Br) follow‑up and standard MRI (T1‑weighted with and without contrast, T2, and FLAIR) imaging at Day 4, 4 weeks, 12 weeks, and subsequently every three months for up to 12 months or until consent withdrawal, documented tumor progression, or death. Tumor response on MRI will be assessed according to RANO criteria for gliomas [21]. At the 1‑month visit, [¹¹C]methionine PET will be performed and evaluated according to PET Response Assessment in Neuro‑Oncology criteria (PET‑RANO), criteria [22] to differentiate pseudoprogression from true progression. GSH‑edited MRS to assess longitudinal changes in intratumoral and normal‑brain GSH levels will be obtained at Day 3, Day 4, and at 1 month.

#### Imaging methods

Baseline MRI, [¹¹C]methionine PET, and GSH‑edited MRS are performed at baseline before the first sulfasalazine dose. On Day 3, GSH‑edited MRS is acquired in the morning (approximately 09:00), after the third sulfasalazine dose (administered at approximately 07:00) but prior to GKRS (scheduled at around 12:00–14:00). This timing captures the pharmacodynamic effect of sulfasalazine immediately before irradiation. On Day 4, GSH‑edited MRS is repeated approximately 24 hours after GKRS to quantify post‑treatment changes in glutathione levels following three days of sulfasalazine exposure and single‑session radiosurgery. A full MRI ± [¹¹C]methionine PET ± GSH‑edited MRS assessment is performed at the 1‑month follow‑up visit to evaluate longer‑term metabolic and structural changes, including contrast enhancement, tumor size, and glutathione dynamics.

Subsequent MRI scans (T1 with and without contrast, T2, and FLAIR) are conducted at 3, 6, 9, and 12 months. PET imaging is repeated only when clinically indicated, such as in cases of suspected pseudoprogression.

GSH‑edited MRS is acquired on a 3T Siemens Biograph mMR system using a MEGA‑PRESS sequence with voxels located in the tumor (nominally 27 mL, with placement tailored to maximize coverage of the individual tumor) and healthy tissue (27 mL voxel in the midline anterior cingulate cortex (ACC), adjusted if necessary to avoid intersection with the tumor volume). Similar positioning will be maintained across visits for each individual. With tumor location and size varying between patients, the MRS voxel is placed judiciously on a per-individual basis to maximize intersection with (GD-enhancing) tumor regions, without extending into the ventricles or non-brain regions. Given the comparatively large volume needed for GSH measurement, voxels typically also overlap with smaller portions of the necrotic/non-enhancing core, peritumoral oedema and healthy tissue. Since the behavior of MRS-measured signals (e.g., decay rates for the metabolite and water reference signals) in the different regions is not well defined, there is currently no meaningful way to adjust for this numerically. Importantly, similar placement is maintained across return visits, so these «partial volume» effects are unlikely to substantially impact longitudinal analysis. Healthy reference voxels are placed medially in the ACC, with minor adjustments (slight shifts) in cases where the nominal placement would have intersected with the tumor volume. All MRS data are analyzed through a common pipeline (Gannet 3.3.2), with configuration adjusted (for the entire dataset) to accommodate factors associated with tumor spectra: most notably, spectral alignment is disabled, as this has been found to function poorly in the presence of extremely strong lipid signals and weak (or absent) signals from typical reference metabolites (NAA, Cr). This is outlined, along with quality control criteria and outcomes for the reconstructed spectra, in the MRSinMRS Table 1[23]^,^ [24].

**Table 1 tbl0001:** An MRSinMRS1 checklist for the Phase I Trial Combining Sulfasalazine and Gamma Knife Radiosurgery for Recurrent Glioblastoma. Protocol Identification Number: SAS-GKRS-TRIAL-01, EUDRACT Number: 2019–002,110-40.

Site (name or number)	Haukeland University Hospital

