### Inclusion and exclusion criteria

The inclusion criteria for this study require that participants must be ≥18 years of age, have histologically confirmed glioblastoma (World Health Organization WHO grade 4) with a first or second recurrence as defined by Response Assessment in Neuro‑Oncology (RANO) criteria, and that they have previously undergone maximal safe resection followed by radiotherapy with concomitant temozolomide. Eligible patients must be suitable candidates for Gamma Knife stereotactic radiosurgery, with a recurrent lesion measuring 3 cm or less (≤ 15 cm³) on MRI obtained within the preceding 30 days prior to treatment. Functional status must be a Karnofsky Performance Status ≥70 and estimated life expectancy >12 weeks. To ensure adequate organ function, baseline laboratory values obtained within 7 days before first study dose must meet all of the following thresholds: absolute neutrophil count ≥1.0 × 10⁹/L without the support of filgrastim; platelet count ≥100 × 10⁹/L; hemoglobin ≥100 *g*/L; total bilirubin <1.5 × the upper limit of normal (ULN), except patients with Gilbert’s syndrome who may enroll if total bilirubin <51.3 µmol/L, alanine aminotransferase (ALT) and aspartate aminotransferase (AST) <3 × ULN; serum creatinine <1.5 × ULN, international normalized ratio (INR) <1.4. At least 4 weeks must have elapsed since any prior systemic anti‑cancer therapy, and all treatment‑related toxicities must have recovered to Grade 1 or lower before enrollment. All participants must provide written informed consent prior to any study‑specific procedures. .

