Although pharmacological data directly demonstrating sulfasalazine penetration of the intact blood–brain barrier are lacking, both the findings from Robe et al. and preclinical experiments detecting sulfasalazine in brain tumor tissue after 3 days of dosing, together with clear radiosensitizing anti‑tumor effects in glioblastoma xenograft models treated with GKRS, indicate that sulfasalazine reaches tumor tissue through the disrupted blood–brain barrier.

Once‑daily dosing is selected for feasibility and consistency with preclinical experiments and facilitates safe administration under direct nurse observation during inpatient hospitalization ensuring adherence. Although pill burden increases across dose levels (3 - 12 x 500 mg tablets), once‑daily administration is operationally simpler than divided dosing while maintaining alignment with the expected radiosensitization window. A single daily dose produces a well‑defined serum concentration peak 3 - 12 hours after ingestion, allowing predictable pharmacodynamic timing relative to GKRS.

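### The Day 3 GSH scan precedes irradiation by 3-5 h and the earliest stated serum peak by 1 h, in a nominal voxel at least 44% outside the lesion, so it may misstate GSH depletion at irradiation

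*Protocol article*

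**What the plan says.** **Timing.** The Imaging methods section places the third dose at about 07:00, the Day 3 GSH-edited MRS at about 09:00 and GKRS at about 12:00-14:00. Of this schedule it says: "This timing captures the pharmacodynamic effect of sulfasalazine immediately before irradiation". The Intervention section places GKRS "approximately 6 hours after participants receive their third and final sulfasalazine dose". The Justification of dose regimen section describes a "serum concentration peak 3 - 12 hours after ingestion" and gives the timing of that peak relative to GKRS as a reason for once-daily dosing. The same section expects three days of dosing to lower tumor GSH gradually.

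**Voxel.** Eligibility requires "a recurrent lesion measuring 3 cm or less", with a volume of at most 15 cm³. The MRS voxel is nominally 27 mL (30 × 30 × 30 mm) with some individual adaptation (Imaging methods and Table 1). The text says that "voxels typically also overlap with smaller portions of the" necrotic core, edema and healthy tissue, that no meaningful numerical correction exists, and that with similar placement at each visit these "effects are unlikely to substantially impact longitudinal analysis".

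**Use.** The outcome is described as intratumoral GSH (Abstract, Aims of study, Secondary outcomes). It is measured at baseline, Day 3, Day 4 and 1 month. The mixed model in Data management and analysis has region, time and their interaction.

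**The concern.** The Day 3 scan is the only GSH measurement between the start of dosing and irradiation, and the article presents GSH-edited MRS as its mechanistic evidence. Two of its descriptions do not fit its own figures: the claim that the scan shows the effect just before irradiation, and the description of the other tissue in the voxel as the smaller part. If both stand, a small Day 3 change could mean no depletion, a scan taken too early, or dilution by tissue outside the lesion, and the report would not help a reader tell these apart. At 1 month there is a further problem. Constant voxel placement does not keep the lesion's share of the voxel constant if the lesion has grown or shrunk, and the planned model has no term for this.

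**Working it through.** **1. Clock times (Imaging methods).**
- Dose 3 to GKRS: 12:00-14:00 minus 07:00 = 5-7 h, midpoint 6 h. This reproduces the interval in the Intervention section.
- Dose 3 to Day 3 MRS: 09:00 − 07:00 = 2 h. This is 1 h before the earliest stated serum peak (3 h) and 10 h before the latest (12 h).
- Day 3 MRS to GKRS: 12:00-14:00 minus 09:00 = 3-5 h.
- Dose 3 to Day 4 MRS, about 24 h after GKRS: 5 + 24 to 7 + 24 = 29-31 h, and after irradiation.

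GKRS falls inside the 3-12 h window after dose 3. No GSH scan does.

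**2. What the Day 3 scan does carry.** If all doses are given at 07:00 (assumed), doses 1 and 2 were taken 50 h and 26 h before the scan. With the stated half-life of 12.7 h, k = ln 2 / 12.7 = 0.0546 per hour. The remainder is exp(−26k) + exp(−50k) = 0.242 + 0.065 = 0.31 of one dose's systemic amount.

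**3. Serum level at the scan relative to 6 h after dose 3.** This is a one-compartment superposition of three daily doses with half-life 12.7 h. Peak time (3-12 h, the stated range) and absorption lag (0-3 h) are assumptions.

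| Assumed absorption | Level at 2 h / level at 6 h |
|---|---|
| No lag, peak at 3 h | 1.12 |
| No lag, peak at 6 h | 0.85 |
| No lag, peak at 12 h | 0.82 |
| No lag, range over peaks 3-12 h | 0.80-1.12 |
| Lag 2-3 h, range over peaks 3-12 h | 0.32-0.60 |

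The ratio lies on both sides of 1. These are serum levels. The documents give no relation between serum level and tumor GSH over time.

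**4. Lesion share of a nominal voxel.** Share = lesion volume / 27 mL.
- 15 mL (entry limit): 15/27 = 55.6%, so 12/27 = 44.4% lies outside the lesion.
- 3 cm sphere: π/6 × 27 = 14.1 mL, share 52.4%.
- 5 mL: 5/27 = 18.5%, so 81% outside.
- 1 mL (a size foreseen under Radiosurgery methods): 3.7%, so 96% outside.
- If the voxel were reduced to 20 mL (assumed), a 15 mL lesion would fill 75%.

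**5. Dilution of a change.** Assume equal GSH per mL in all tissue and no change outside the lesion. Measured fall = true fall × share.
- True fall 30%: 0.30 × 0.556 = 16.7% at 15 mL; 0.30 × 0.185 = 5.6% at 5 mL.
- True fall 40%: 0.40 × 0.556 = 22% at 15 mL; 0.40 × 0.185 = 7% at 5 mL.

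**6. Volume effect at 1 month.** With share f and tumor-to-normal GSH ratio r, voxel GSH = f·r + (1 − f). For illustration, let a 15 mL lesion halve, so that f goes from 0.556 to 0.278 with tissue GSH unchanged.
- r = 2: 1.556 to 1.278, a change of −18%.
- r = 0.5: 0.722 to 0.861, a change of +19%.

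The values of r and the halving are assumptions, and the sign depends on r.

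**The case against.** The 3-12 h figure is a serum peak, whereas the disputed sentence concerns a pharmacodynamic effect that the protocol expects to build up over three days. A reader might infer that the Day 3 scan fails to measure drug-induced depletion, or that it understates depletion at irradiation. The documents support neither. The scan carries doses 1 and 2 and the start of dose 3, and the serum ratio in the working can exceed 1. This stands, and it limits the timing point to a possible misstatement of unknown direction and size.

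The 56% share is not a strict ceiling on tumor content. The voxel may be adapted, and the Limitations section calls glioblastoma diffuse, so tissue outside the measured lesion is not necessarily free of tumor. This stands too: the figure is the lesion share of a nominal voxel.

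Partial volume is disclosed and placement is held similar. Dilution shrinks the baseline-to-Day 3 change but does not cancel it. That defense is reasonable over a few days but does not extend to 1 month. A reader might conclude that the 1-month change is purely a volume artifact. The documents do not show this, since the example rests on assumed ratios and shrinkage.

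There are also fair objections to the remedy. A frame and stereotactic MRI must come before GKRS, and no frame time is given, so a later slot may not be feasible. Table 1 reports signal-quality medians for lesion and healthy voxels, which suggests that spectra already exist; a new slot would then mix scan times across dose cohorts. Lesion fraction is itself affected by treatment, so adjusting for it in the main model could remove real effect.

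**Conclusion.** The point holds in limited form. The Day 3 scan, 2 h after dose 3 and 3-5 h before GKRS, cannot be said to show the effect just before irradiation, and it precedes the serum peak that the protocol itself uses to time GKRS. It may misstate depletion at irradiation; the documents fix neither direction nor size. With a nominal voxel, at least 44% of the volume lies outside the lesion, and 81% for a 5 mL lesion, so describing the other tissue as smaller portions is wrong. A measured change is diluted roughly in proportion to the lesion share, if tissue GSH is equal and the surroundings do not change. At 1 month part of any GSH change may be a volume effect. The consequence is confined to the mechanistic claim: GSH is a secondary outcome, summarized descriptively with acknowledged low power, and has no role in dose escalation or the MTD.

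**What to change.** Reconcile the Justification of dose regimen and Imaging methods sections as follows.

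1. Withdraw the claim that the Day 3 scan shows the effect just before irradiation, and state instead that it is taken about 2 h after dose 3 and 3-5 h before GKRS. Alternatively, with dosing unchanged, scan closer to GKRS, but only if logistics allow and scan times are not mixed across cohorts.
2. Record and report the dose-to-scan and scan-to-GKRS intervals for each patient.
3. Replace the description of voxel content with the enhancing-lesion fraction of each voxel, measured on MRI already acquired. This is a geometric quantity and needs none of the signal-decay assumptions that the protocol rightly declines to make.
4. Label the outcome tumor-voxel GSH.
5. Take baseline to Day 3 as the main mechanistic contrast.
6. Use lesion fraction in a sensitivity analysis of the 1-month change, not as a covariate in the main model.

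The cost is some segmentation work and a more modest mechanistic claim. Moving the scan, if chosen, would also tighten the schedule before frame placement.
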